### Recruitment

We will advertise participation and assess participants for eligibility until achieving the target sample size. There is an estimated number of 55,000 GPs in Germany [32]. Based on an assumed response rate of up to 5% observed in similar studies [33], we targeted to contact at least 2,000 GPs in order to achieve a sample of *N* = 100 GPs in an 18-month time window. Recruitment and data collection started on July 23, 2024, following the trial’s preregistration, and are both expected to be completed until November 1, 2025. Thus, results are expected by the end of 2025.

### Assignment of interventions

Participants will be randomly assigned to either the control or intervention conditions with a 1:1 allocation as per a specified randomization schedule. Randomization will be conducted electronically. Blinding of the researcher conducting the interviews was deemed infeasible, but participants will be blinded as per the different study conditions.

### Data collection methods

All quantitative and qualitative data will be collected pseudonymously via electronic data capture tools (see below). Regarding primary outcomes, the cognitive facet of stigma (i.e., stereotypes) will be operationalized in terms of knowledge deficits regarding EDs in boys and men. We will construct and pilot a set of ten single-choice items (with five alternative answers each, from which one correct answer must be selected). The items will be collaboratively constructed based on literature search and intensive discussions within our team of experienced scientists and clinicians and the lived experience advisory board members. The global score will be calculated as the sum of correct answers over all items. The affective facet of stigma (i.e., prejudice) will be assessed using an adapted version of the validated German [25] Opening Minds Stigma Scale for Health Care Providers (OMS-HC) [26] replacing “person with a mental illness” with “men with an eating disorder”. The OMS-HC includes 15 self-report items rated on a 5-point Likert scale from 1 (*strongly disagree*) to 5 (*strongly agree*). The attitudes subscale score will serve as the primary dependent variable regarding the affective stigma facet. The behavioral facet of stigma will be assessed with three adapted items of the German version [34] of the General Self-Efficacy Scale (GSE) [27] (“I can remain calm when facing difficulties in the treatment of men with eating disorders because I can rely on my coping abilities”, “I am confident that I could deal efficiently with unexpected events in the treatment of men with eating disorders”, “When I am confronted with a man with an eating disorder, I can usually find several solutions”). Responses are made on a 4-point scale ranging from 1 (*not at all true*) to 4 (*exactly true*). An overall score will be computed as the sum of the three items.

Short-term implementation outcomes, i.e., acceptability, feasibility, appropriateness, and adoption will be assessed with one item each (“How satisfied are you with this module?”, “How do you rate the practical suitability of the module content?”, “How do you rate the relevance of the module for your day-to-day work?”, “How would you rate your willingness to incorporate the module content into your work?”). The items are all rated on 5-point Likert scales in grade marks from A to E (A = 1/*very good* to E = 5/*unsatisfactory*). These items, which are assessed both after each module and at the end of the overall training course, are complemented by two open-ended questions aimed at identifying areas for improvement (“What would you like to improve about this module?”) and capturing any additional feedback (“Is there anything else you would like to say?”).

A consensus on intermediate-term implementation outcomes will be derived from responses to open-ended questions obtained during telephone-based qualitative interviews, conducted using a semi-structured interview guideline. Intermediate-term implementation outcomes will be assessed in terms of fidelity (e.g., changes in awareness, attitudes and sensitization), penetration (e.g., modified history taking procedures, changes in the number of identified eating disorder cases in men, number of referrals to psychiatric, psychosomatic or psychotherapeutic treatment), and sustainability (e.g., changes in treatment practice such as the introduction of routine screening questions on eating behaviors, utilization of standardized diagnostic instruments, or medical case management). The interview guideline will be developed based on extensive literature search and critical discussions between the research team and advisory board members regarding both conceptualization and operationalization and considering the specific context of primary care physicians.

The secondary outcome stigma-related perceptions of EDs in men will be assessed with a previously developed set of seven items [8] based on a qualitative analysis of testimonials of men with EDs (e.g., “Eating disorders are women’s diseases”, “It is better for a man to not admit having an eating disorder”). The items are rated on a 4-point scale from 1 (*completely disagree*) to 4 (*completely agree*), and aggregated as means such that higher scores indicate higher perceived stigma of EDs in men.

Assessed sociodemographic baseline features include participants’ age, gender, sexual orientation, marital status, German language proficiency, migration background, and self-identification as part of a minority group. We further assess the job situation and characteristics of GPs (current job situation, federal state of main job activity, size of the city of main job activity, and specific setting details). Students will be asked similar questions as GPs regarding their current medical training (e.g., current semester, desired medical specialization). GPs will also be presented questions regarding their professional medical background, including duration of employment as a medical professional, specialty areas, years of experience, current position in primary care, and work experience in psychiatry. We will examine these variables for group differences and, if necessary, include them as covariates in the analyses.

For exploration, we will also at baseline assess attitudes towards mental health in GPs and medical students (e.g., practice and attitude towards the assignment of diagnoses of mental disorders, utilization of standardized diagnostic instruments, frequency of encountering patients with mental health issues, attitudes towards the referral to specialized mental health treatment facilities), and personal experiences with mental disorders and associated impairments (e.g., living with a person with an ED, having oneself received an ED diagnosis and/or treatment, living with disability). Furthermore, we will ask participants for their professional experiences with individuals with EDs at baseline.

Finally, baseline measures include the Traditional Masculinity-Femininity Scale (TMF) [29]. This scale measures self-perceived core aspects of one’s gender role-associated self-concept regarding masculinity and femininity based on traits, interests, appearance, and behaviors on two separate subscales with six items each, using two 4-point Likert scales ranging from 1 (*not at all masculine*) to 4 (*totally masculine*) and 1 (*not at all feminine*) to 4 (*totally feminine*), respectively.

To promote participant retention, participants will receive reminder emails (see section “Participant Timeline”) and a compensation for completing the survey and online intervention (i.e., monetary reimbursement for GPs, participation in the prize draw for online vouchers for medical students). Further, the survey is set up so that most questions cannot be skipped to proceed or submit the survey, with in-built reminders of unanswered items.

### Data management

Data management for quantitative data will be realized using jsPsych [35] and the Moodle learning management system’s [36] version 4.4 built-in survey modules, hosted by Ruhr-University Bochum’s IT services department. Qualitative data will be collected by means of audio recordings, ensuring privacy of the participants, since no video is recorded. The interviews will be transcribed using noScribe [37] version 0.6, a locally operated AI transcription tool based on Whisper [38], again meticulously ensuring data protection and privacy. The automated transcription will afterwards be proofread by research assistants, trained in conducting and transcribing qualitative interviews in an iterative process. All systems connected to the internet employ SSL-encryption for secure data capture and transfer. Personal data entered upon registration will be stored separately from outcome data; all outcome data (e.g., questionnaire data, interview audio files and transcripts) will be pseudonymized for the duration of the study and will be fully anonymized upon study completion.

Data will be assessed for completeness, plausibility, quality (including an attention check via the item “Have you watched the full video?” after each video/module as well as a double-participation check using the item “Have you previously completed our “Eating disorders in boys and men” course?”), and range validation.

### Data analysis

Qualitative data analyses will be conducted using MAXQDA [39] version 24.5.1. Quantitative data analyses will be performed using R [40] and SPSS [41].

Regarding quantitative data, we will conduct two sets of analyses. These will be per-protocol analyses and intention-to-treat analyses. For the per-protocol analyses, we will compute a 2 (intervention vs. wait-list control) x 3 (timepoint) mixed-measures ANOVA per each outcome and participant group, accounting for the two groups (intervention vs. wait-list control group) and the three time points of quantitative assessment. The intention-to-treat analyses will be conducted using a corresponding 2 x 3 mixed model, with by-participant random intercepts (and slopes, if justified by the data). We will also conduct contrast analysis for the 2 x 3 design (1 −1 −1 1 1–1) to directly test the predicted interaction pattern. The change from pre- to post-intervention will be estimated with a paired-samples t-test for any participant that completed the intervention. Quantitative implementation data will be aggregated descriptively and compared between groups.

The per-protocol analysis will use case-wise exclusions in case of missing data. In case of dropout/case exclusions, the ITT mixed model will be conducted with and without multiple imputation based on predictive mean matching functioning as a sensitivity analysis.

The qualitative data collected in the beginning (focus group, panel discussion) and after the intervention (during telephone-based interviews) will be subjected to systematic qualitative thematic analyses based on the Braun and Clarke method [42,43]. Coding will be performed by two independent researchers. Braun and Clarke’s [42] approach to qualitative thematic analysis follows a six-phase iterative and reflective process that evolves over time, requiring researchers to deeply engage with the data and continuously move back and forth between phases. The process begins with (1) familiarization with the data, where researchers immerse themselves in the data through repeated reading and note-taking to identify initial patterns. Next, (2) initial codes are systematically generated to capture meaningful data features. These codes are then (3) grouped into broader themes that represent meaningful relationships within the data. The identified themes (4) are then reviewed to ensure coherence and accurate representation of the dataset, resulting in further refinement and the generation of a thematic ‘map’ of the analysis. Once finalized, (5) themes are clearly named and defined. The final phase involves (6) synthesizing the findings into a cohesive report by the selection of vivid, compelling extract examples, final analysis of selected extracts, and relating back of the analysis to the research question and literature. Qualitative data will be transcribed and fully anonymized before the analysis. Regarding the telephone-based interviews, the individual subject’s report will be used as the unit of analysis. The transcripts will be coded and analyzed in MAXQDA [39] by two independent researchers as well as trained research assistants, such that each transcript will be coded by two coders independently. To establish a common understanding of the research questions and methodology, we will hold a meeting with all team members before commencing the qualitative data analysis. The findings from both the quantitative and qualitative phases will be integrated during the final data integration stage.

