### Participant timeline

Individuals interested in taking part in the study can self-enroll via a webform on the project website (https://maennermitessstoerung.rub.de), which is referenced as link and QR code in leaflets and mailings. At enrollment (-t_1_), participants will answer baseline and sociodemographic questions, undergo eligibility assessment and be allocated to their respective participant group (GP or medical student) and study arm (intervention or wait-list control). Participants allocated to the wait-list control groups will be informed that they need to wait 14 days for the online training. Participants of the wait-list control groups will be meanwhile invited to a quantitative pre-participation assessment at t_1_ within the two-week waiting period, after which they will receive the personalized login credentials for the online learning platform to administer a quantitative pre-intervention assessment at t_2_ (end of the waiting period), then followed by the actual online training and a quantitative post-intervention assessment at t_3_. By contrast, participants allocated to the intervention group directly receive personalized login credentials for the learning platform at t_1_ (enrollment) and administer pre-intervention assessments before participating in the online training, followed by a quantitative post-intervention assessment at t_2_. Intervention group participants will be contacted to administer a quantitative post-participation/follow-up assessment at t_3_ another 14 days after they have completed the online training. Both groups will have 14 days to complete the training. To minimize the risk of participant dropout, participants will receive reminder emails on several time points during their participation (a reminder for completing the pre-survey 1 week after receiving the pre-survey link, a reminder for completing the online training one week after receiving login credentials and another reminder two days before termination of the 14-days participation time window, and a reminder for the post-survey 1 week after receiving the post-survey link). This procedure applies to both GPs and medical students allocated to the respective study arms. Finally, selected participants of the GP groups are invited to a qualitative telephone interview (t_4_) about four months after completion of the online training and respective quantitative assessments (see Fig 2).

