### Sample size

To determine the appropriate sample size for the planned quantitative analysis (e.g., a 2x3 repeated measures ANOVA with a within-between interaction), an a priori power analysis was conducted using G*Power 3.1.9.7 software [30]. The aim was to achieve a power of.80 [31] with an alpha level of.05. A small-to-medium effect size (*f* = 0.15) as found in prior ED-related anti stigma research [15] and moderate correlation (*r* = .50) among the repeated measures were assumed, as observed in similar fields and due to practical significance considerations. The epsilon (ε) was set to 1, assuming sphericity, which is the most conservative scenario. Using these parameters, the G*Power analysis indicated that a total sample size of 74 participants is required, i.e., a minimum of 37 participants per group. Considering dropouts and cases with insufficient plausibility or quality of data, the study aims for an experimental group of approximately 50 GPs and a wait-list control group with further 50 GPs. To estimate the needs and benefits of future curricular use, the intervention will also be made accessible to approximately 50 medical students in their clinical training year. For the qualitative analyses, up to ten participants with lived experience of EDs and additional GPs for the pre-implementation focus group and panel discussion, and up to 50 GPs for the telephone-based qualitative post-implementation interviews were considered sufficient.

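### The 2 x 3 models use the t1 outcome score only as a free outcome level, so the controlled t2 comparison gives up precision that baseline adjustment would recover

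*Protocol article*

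**What the plan says.** The Data analysis section sets one model for each analysis set. The per-protocol model is a mixed ANOVA for each outcome and participant group, "accounting for the two groups (intervention vs. wait-list control group) and the three time points of quantitative assessment". For the other set, "The intention-to-treat analyses will be conducted using a corresponding 2 x 3 mixed model, with by-participant random intercepts", with random slopes if the data justify them. A contrast over the six cells and an uncontrolled paired t-test in those who completed training are added.

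The Participant timeline gives the order of events. Intervention participants "administer pre-intervention assessments before participating in the online training, followed by a quantitative post-intervention assessment at t_2". Wait-list participants are assessed at t1 during the waiting period and again at its end (t2). They are then trained and assessed at t3. So t2 is the only time at which one arm has been trained and the other has not.

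The Sample size section sizes "a 2x3 repeated measures ANOVA with a within-between interaction", with f = 0.15, alpha .05, target power .80 and sphericity, and states "moderate correlation (*r* = .50) among the repeated measures were assumed". The result is 74 in total, with about 100 GPs and about 50 students to be recruited.

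The article nowhere uses the t1 outcome score as a covariate or gives the arms a common t1 mean. Its covariate rule, under Data collection methods, concerns sociodemographic, job and professional-background variables, and applies only if a check for group differences makes it necessary.

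**The concern.** When each arm has its own t1 mean, the group-by-time effect from t1 to t2 subtracts the whole observed baseline difference between arms. With a correlation of .50 and equal variances, the best prediction of t2 from t1 carries over only half of that difference. Subtracting all of it adds noise that a t1 covariate would remove.

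At stake is the precision of the trained-versus-untrained comparison, which is what the third objective (effect on knowledge, attitudes and self-efficacy) rests on. The trial is small, each participant group is analysed separately, and the baseline scores are collected anyway.

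**Working it through.** **Inputs.** From the Sample size section: f = 0.15, r = .50, alpha .05, epsilon 1, N = 74, target 100 GPs, about 50 students. Allocation is 1:1 (Assignment of interventions). My assumptions: equal variances, complete data and, for the main figures, arms that differ only at t2.

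**1. The plan's figure.** For the within-between interaction, noncentrality = f² x N x 3/(1 − r) = 0.0225 x 74 x 3/0.50 = 9.99, on 2 and 144 degrees of freedom. Power is .806; at N = 72 it is .795. The stated 74 is correct. At N = 100 the power is .914.

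**2. What f = 0.15 means at t2.** With arm differences of 0, d, 0 at t1, t2, t3 (in SD units), f² = d²/18. So d = 0.15 x √18 = 0.636 SD.

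**3. Variance of the t2 comparison, per participant.**
- Difference in change: 2(1 − r) = 1.00.
- t2 adjusted for t1: 1 − r² = 0.75.
- t2 alone, ignoring t1: 1.00.

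The ratio of standard errors is √(1.00/0.75) = 1.155, about 15% wider. At r = .50 the change score does no better than t2 alone.

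**4. Standard errors at N = 74.** Change: √(1.00 x 4/74) = 0.232 SD. Adjusted: √(0.75 x 4/74) = 0.201 SD.

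**5. Power, d = 0.636, r = .50 (noncentral t; noncentral F for the 2-df test).**

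| N analysed | Change | Adjusted | Planned 2-df test |
|---|---|---|---|
| 74 | .771 | .877 | .806 |
| 100 | .883 | .953 | .914 |
| 50 (students) | .597 | .721 | .624 |

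A simulation of 20,000 trials at N = 74 gave .767 (change) and .865 (adjusted). By the normal approximation, .80 power needs 39 per arm with change scores and 30 per arm with adjustment.

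**6. Other correlations, N = 74, same d.** At r = .30: .63 (change) against .81 (adjusted). At r = .70: .94 against .97, a gain of about 3 points.

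**7. If the intervention arm trails at t3.** Let it be behind by a fraction k of the t2 effect, so the arm differences are 0, d, −kd. Keep f = 0.15, r = .50, N = 74. Then f² = d² x [1 + k² − (1 − k)²/3]/12.

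| k | d at t2 | Change | Adjusted | Planned 2-df test |
|---|---|---|---|---|
| 0 | 0.636 | .771 | .877 | .806 |
| 0.25 | 0.555 | .654 | .777 | .806 |
| 0.50 | 0.481 | .533 | .654 | .806 |

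The adjusted analysis beats the change score in every row. Its advantage over the 2-df test is gone at about k = 0.20 (.800 against .806).

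**The case against.** The strongest reply is that the article does not name the t1-to-t2 change contrast as its test. It names and sizes the 2-df interaction, which reaches its stated power. That stands: against this test the gain is 7 points at 74 and 4 at 100, not the 10 or 11 points found against the change score. Those 7 and 4 points also require equal arms at t3. The timeline places t3 about 14 days after training in one arm and directly after training in the other, so some fading is plausible, and step 7 shows the advantage reversing. In that case, though, the extra power of the 2-df test comes from fading and not from trained versus untrained, and the test yields no single effect estimate.

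A second reply is that the planned contrast already covers the predicted pattern. A pure interaction contrast, t2 against the mean of t1 and t3, would indeed have power .881 at N = 74, but only if the arms are equal at t3. The printed weights are not that contrast. Read group by group, their sum of squares of 6 splits into 4.00 for time, 0.67 for group and 1.33 for interaction.

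A third reply concerns t1 itself. Wait-list participants complete it after learning that they must wait, so equal t1 means are not guaranteed by the design. This stands and limits the remedy.

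A reader might also infer that the planned analysis is biased, because a chance t1 imbalance shifts the change score. A one-standard-error imbalance (0.23 SD at 37 per arm) shifts it by about 0.12 SD. That inference is not supported. Over randomisations the change score is unbiased, and the shift is already in the wider standard error: the excess variance, 1.00 − 0.75 = 0.25, equals (1 − r)², which is the imbalance term. It is not a second harm.

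**Conclusion.** The point holds as a loss of precision in an otherwise valid analysis; nothing the article states here is wrong. At r = .50 the controlled t2 comparison has a standard error about 15% wider than the collected data allow. With arms that differ only at t2, adjustment raises power for that comparison from .77 to .88 at 74 analysed and from .88 to .95 at 100.

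A reader might infer that the trial falls about 10 points short of its planned power. It does not: the sized 2-df test keeps .81. The gain over that test is about 7 points (4 at 100) and depends on the arms being equal at t3. The gain over raw change does not need equality at t3, but it shrinks to about 3 points if the true correlation is .70. The article reports no observed correlation for these adapted scales.

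**What to change.** In the Data analysis section, keep the 2 x 3 models and add one sentence. For each outcome and participant group, the training effect is estimated as the t2 difference between arms adjusted for the t1 score of the same outcome (ANCOVA), in both analysis sets, with the unadjusted 2 x 3 result reported beside it.

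The mixed model with t1 arm means constrained equal would keep participants with a missing t2 in the intention-to-treat set. Use it only if t1 can be treated as unaffected by allocation, and state that assumption, given when the wait-list arm completes t1.

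The cost is that sentence and a small change to the R or SPSS code; no new data or participants are needed. The downside is small: adjustment relies on t1 being a pre-training value comparable between arms, which is why the unadjusted result should stay visible.

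### The intention-to-treat mixed model rests on random intercepts with data-driven slopes; if the three time points are not equally correlated, contrast standard errors can be wrong in either direction

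*Protocol article*

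**What the plan says.** Under Data analysis, the protocol article states: "The intention-to-treat analyses will be conducted using a corresponding 2 x 3 mixed model". It models the within-participant dependence "with by-participant random intercepts (and slopes, if justified by the data". The model mirrors the per-protocol ANOVA, which accounts for two groups and "the three time points of quantitative assessment". Time is therefore a three-level factor, with one score per participant, outcome and time point. A six-weight contrast is added "to directly test the predicted interaction pattern". No other covariance structure is named, and no rule says when slopes count as justified or on which variable they are placed.

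Under Participant timeline, the intervention arm trains between t1 and t2. The wait-list arm has its pre-intervention assessment at t2, "then followed by the actual online training and a quantitative post-intervention assessment at t_3".

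Under Sample size, the calculation uses one common correlation of .50 and epsilon = 1, described as "assuming sphericity, which is the most conservative scenario".

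**The concern.** A mixed model with a random intercept and independent, equal-variance residuals implies compound symmetry: one variance and one correlation for all three time points in both arms. Every pairwise change then gets the same standard error. The staggered training is a reason to doubt this, because individual responses to training may weaken the correlation over the trained interval, and that interval differs by arm.

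The slope option does not reliably repair this. Fully correlated slopes on the time factor cannot be separated from the residual. A linear-time slope is a poor match to a step-shaped response. At stake are the standard errors, confidence intervals and p-values of the analysis that is meant to protect the randomised comparison, for every outcome and both participant groups. The Sample size section relies on the same sphericity assumption and describes it as safe when it is not.

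**Working it through.** **1. The plan's own sample size.** Inputs from Sample size: f = 0.15, r = .50, alpha .05, power .80, k = 2 groups, m = 3 time points. For the within-between interaction:

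λ = f²·N·m·ε/(1 − r), df1 = (k − 1)(m − 1)ε, df2 = (N − k)(m − 1)ε.

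At N = 74:

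| ε | λ | df1, df2 | Power at N = 74 | N for power .80 |
|---|---|---|---|---|
| 1 | 0.0225 × 74 × 3/0.5 = 9.99 | 2, 144 | .806 | 74 |
| .75 | 7.49 | 1.5, 108 | .719 | 90 |
| .5 | 5.00 | 1, 72 | .597 | 120 |

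The stated 74 is reproduced (the smallest even N). Power falls as ε falls from 1 to its lower bound of 1/(m − 1) = .5, so ε = 1 is the least conservative choice.

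**2. Parameter count.** A 3 x 3 covariance has 6 distinct elements.
- Random intercept plus residual: 2 parameters.
- Intercept plus linear-time slope, correlated: 4, estimable.
- Intercept plus uncorrelated factor slopes: 4, estimable.
- Intercept plus fully correlated factor slopes plus residual: 6 + 1 = 7, rank 6, not identifiable.

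**3. t1–t2 arm difference, both arms sharing the same covariance.** The correlations are assumptions, because the documents give only r = .50. SDs are set equal. With complete balanced data a random-intercept fit uses the mean correlation r̄, so

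model SE / true SE = √[(1 − r̄)/(1 − r12)], and asymptotic type I error = 2Φ(−1.96 × ratio).

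| r(t1t2)/r(t2t3)/r(t1t3) | r̄ | Ratio | Type I error | Simulated 95% CI coverage |
|---|---|---|---|---|
| .5/.5/.5 | .500 | 1.00 | 5.0% | – |
| .3/.7/.4 | .467 | √(.533/.7) = 0.87 | 8.7% | 91.7% |
| .7/.7/.4 | .600 | √(.4/.3) = 1.15 | 2.4% | 97.5% |
| .7/.3/.4 | .467 | √(.533/.3) = 1.33 | 0.9% | 98.9% |

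Coverage is from 20,000 simulated trials with 37 per arm and no effect. Epsilon in the three unequal patterns is .80 to .83.

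**4. Does a linear-time slope help?** Its maximum-likelihood fit to the same three patterns gives ratios of 0.85, 1.00 and 1.29. It is right in one pattern and no real improvement in the other two.

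**5. Correlations mirrored between arms.** Intervention .3/.7/.4, wait-list .7/.3/.4, so the correlation is low over each arm's own training interval.
- *t1–t2 arm difference.* True variance (times n) is 2(.7) + 2(.3) = 2.00. The model gives 2 × 2(.533) = 2.13. Ratio 1.03, type I error 4.3%.
- *Printed contrast*, read as intervention (1, −1, −1) and wait-list (1, 1, −1). True variance is (3 − 2r12 − 2r13 + 2r23) + (3 + 2r12 − 2r13 − 2r23), each with its own arm's values: (3 − .6 − .8 + 1.4) + (3 + 1.4 − .8 − .6) = 6.00. The model gives 2(3 − 2r̄) = 4.13. Ratio √(4.13/6.00) = 0.83, type I error 10.4%.
- *Pooled unstructured covariance* (r12 = r23 = .5, r13 = .4): 2.2 + 2.2 = 4.40. Ratio 0.86, type I error 9.3%.
- *Arm-specific unstructured covariance:* about 5% in simulation.
- *Opposite mirroring* (intervention .7/.3/.4, wait-list .3/.7/.4): true variance of the printed contrast is 1.4 + 1.4 = 2.80. Ratio √(4.13/2.80) = 1.21, type I error 1.7%.

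A milder mirrored pair (.4/.7/.4 with .7/.4/.4) gives 9.8% for the printed contrast under a random intercept and, in simulation, 7.8% under a pooled unstructured covariance.

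**The case against.** The strongest reply is that nothing in the documents shows unequal correlations. The only correlation given is a common .50, and at that value the random-intercept model is exact. This stands: size and direction are conditional on assumed values.

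Two stronger readings are tempting, and the documents support neither.
- A reader might infer that the slope option cannot be fitted, leaving only the random intercept. That is true only of fully correlated factor slopes. Linear-time, uncorrelated or trained/not-trained indicator slopes are estimable, and the text does not say which is meant. Even in the over-parameterised model only the split between random effects and residual is undetermined; the implied 3 x 3 covariance is saturated. The harm comes from retreating to a simpler structure.
- A reader might infer that the t1–t2 arm comparison is anticonservative because training falls in different intervals. The 13% shortfall requires both arms to share the low t1–t2 correlation. When that pattern is mirrored, as staggered training would suggest, the shortfall disappears. Two of the three unequal shared patterns are conservative for this contrast.

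It can also be said that covariance structure, degrees of freedom and sphericity corrections belong in an analysis plan that is not shown. That holds for the last two as omissions. The random-effects structure is different: the article states it, and leaves the choice within it to the data without a rule. Finally, the article does not tie the printed contrast to the mixed model's error term, and its weights sum to −1 and +1 within the arms, so it also carries main effects. The 10% figure therefore assumes that this contrast is tested within the model.

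**Conclusion.** The point holds in a conditional form. The stated structure is either compound symmetry or a slope model that is over-parameterised or restrictive. It is correct if the three correlations and variances are equal in both arms, as the sample size calculation assumes. If they are not, standard errors err in either direction. For the t1–t2 arm difference the error runs from 13% too small to 33% too large (type I error about 1% to 9%) under the assumed shared patterns. For the printed contrast, type I error is about 10% when correlation is weakest over each arm's own training interval, and below 2% under the opposite mirroring. These figures assume equal SDs, complete data, 37 per arm in the simulations, independent residuals, and the row-wise reading of the printed weights.

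Separately, and without any such assumption, the Sample size section misdescribes epsilon = 1. Power at N = 74 is .81 there but .72 at .75 and .60 at .5. The figure of 74 itself is correct for the inputs stated.

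**What to change.** Replace the choice between random intercepts and slopes with one specification: categorical time, group, group x time, and an unstructured 3 x 3 within-participant covariance, arm-specific where it converges and pooled otherwise, with Kenward-Roger or Satterthwaite degrees of freedom. Apply the Greenhouse-Geisser correction in the per-protocol ANOVA. Under Sample size, correct the description of epsilon = 1 and report power at lower values.

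The cost is a sentence or two of text. Statistically, the pooled version estimates four more covariance parameters than the random intercept (6 against 2) and the arm-specific version ten more (12 against 2), with slightly fewer degrees of freedom. The pooled fallback does not fully protect the printed contrast if the arms differ, so the report should say which version was fitted. The target of 74 at epsilon = 1 does not change.
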